### Outcome measures

The primary outcome measure for the FELL-HD trial is the number of adverse events (AEs) attributable to felodipine. An AE is any untoward medical occurrence in a participant that may or may not have a causal relationship to the treatment. Recording of AEs starts from the point of informed consent at the screening visit regardless of whether a participant has started the treatment or not.

Exploratory outcome measures of the trial include:

Changes in clinical measurements of HD using validated motor and cognitive assessment tools between baseline visit (week 0) and end of the trial (week 62).Change on a range of MRI volumetric measures between baseline (week 0) and end of the trial (week 62).

In the sample-study FELL-HD-s, the primary outcome measure is the change in mHTT levels in the blood between baseline (week 0) and end of the trial (week 62). The secondary outcome measurement is the change in neurofilament light chain (NFL) levels in the blood between baseline (week 0) and end of the trial (week 62).

Exploratory outcome measures of the FELL-HD-s-study include:

Change in level of felodipine in the blood between baseline and week 62.Change in level of felodipine in the CSF between baseline and week 57.Change in mHTT levels in the CSF between baseline and week 57.Change in NfL levels in the CSF between baseline and week 57.Change in level of glial fibrillar acidic protein (GFAP) in the blood between baseline and week 62.Change in level of GFAP in CSF between baseline and week 57.

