Other non-motor aspects of HD will be evaluated using the Problem Behaviours Assessment-short), which is a semistructured interview used to rate behavioural symptoms of HD. The assessment looks at depression, anxiety, irritability, aggression, apathy, perseverative thinking, obsessive–compulsive behaviours, delusions, hallucinations, disorientation and will be administered by a trained member of the trial team.^13^ We will also use the Columbia Suicide Severity Rating Scale to rate if there is any suicidal ideation and behaviour on a scale ranging from ‘wish to be dead’ to ‘active suicidal ideation with a specific plan and intent’, participants will answer yes or no to the questions and any that have an answer of yes, more details will be captured. This assessment will be administered by a trained member of the trial team.^14^ Finally, the Hospital Anxiety and Depression Scale will be used which is a self-rating scale to measure anxiety and depression.^15^

Vital signs will be assessed closely, in particular, measurement of blood pressure due to felodipine being an antihypertensive drug. Vital signs (blood pressure, pulse, respiratory rate and body temperature) will be measured at all clinic visits. Participants will also be asked to take weekly blood pressure readings at home and complete a diary that will be reviewed at all clinic visits by the trial team. Participants will be required to inform the trial team if blood pressure readings drop below 90/60 mm Hg or if they experience symptoms of low blood pressure, where further monitoring may be required as decided by the trial team.

Participants’ concomitant medications will be recorded while they are on the trial (including any dose changes), and participants may continue to take all regular medications as prescribed. Participants on any medications that contraindicate the use of felodipine will be excluded from participating in the trial.

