#### Biosample collection and processing

As part of the FELL-HD trial, full blood count, liver function tests and urea and electrolytes samples will be taken at every clinic visit and analysed at the Laboratory Research Services in Addenbrooke’s Hospital.

If participants also consent to the FELL-HD-s substudy, 7.5 mL of blood will be collected and tested for HIV, HBV and HCV status to confirm eligibility. Starting at the baseline (week 0) visit and every 8 weeks up to week 40 and then at week 57 and week 62, up to 75 mL of blood will be collected for analysis of markers of disease, as well as levels of felodipine in the blood.

Samples will be taken in two different types of blood collection tubes depending on which laboratories the specimens will be sent to. Two samples will be taken in 8 mL sodium heparin cell preparation tubes and centrifuged at centrifugal force (RCF) 1500×g for 30 min at room temperature for extraction of plasma. Three samples will be taken in 6 mL K2E blood collection tubes and centrifuged at RCF 1300×g for 10 min at 4°C for extraction of plasma.

If consented, CSF will be collected via lumbar puncture at baseline (week 0) before treatment commences and week 57, 1 week prior to the end of treatment. The CSF will be used to assess levels of felodipine, NfL, mHTT and GFAP. CSF will be centrifuged at RCF 400×g for 10 min at 4°C. After spinning, the CSF supernatant will be separated from the CSF cells and stored.

All aliquots for blood and CSF will be stored at −80°C until the end of the trial where they will then be sent to the analysing laboratory which will look at the above protein levels.

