### Statistical methods

A statistical analysis plan (SAP) will be finalised and approved before the commencement of the analysis. The analysis will be performed on the modified intention-to-treat population, which includes all eligible participants who had at least one dose of investigational treatment and were not replaced during the trial. Participant data will be analysed according to their allocated cohort. The primary outcome is felodipine-related AEs, therefore, missing data are not expected. In all analyses, no imputation will be performed.

Participant data will be summarised by cohort. For the primary endpoint, no formal hypothesis testing will be performed. The statistical analysis will be mostly descriptive, with the number of felodipine-related AEs summarised by dosage for each cohort. All the exploratory endpoints described in the outcome measurement section will be summarised, and a significance test will be performed between baseline and week 57/62, using a paired t-test as the primary analysis and a Wilcoxon signed-rank test as the sensitivity analysis. No formal subgroup analysis will be performed. This trial has no predetermined ending criteria or formal interim analysis.

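### The significance test on CSF felodipine compares an on-treatment level with a pre-dose value expected to be zero, so its p-value says almost nothing about how much drug reaches the CSF

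*Protocol article*

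**What the plan says.** Four statements in the protocol article bear on this point.

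- **Outcome measures** lists among the FELL-HD-s exploratory outcomes "Change in level of felodipine in the CSF between baseline and week 57". The matching blood outcome is the change in felodipine level from baseline to week 62.
- **Biosample collection and processing** sets the timing: "CSF will be collected via lumbar puncture at baseline (week 0) before treatment commences and week 57, 1 week prior to the end of treatment". Research blood, including felodipine levels, is scheduled in that section at week 57 and at week 62.
- **Statistical methods** states "All the exploratory endpoints described in the outcome measurement section will be summarised" and continues that "a significance test will be performed between baseline and week 57/62, using a paired t-test as the primary analysis", with a Wilcoxon signed-rank test as sensitivity analysis. In Outcome measures, week 57 is used only for CSF outcomes, so the reference to week 57 brings CSF felodipine under this rule. Data are analysed by allocated cohort.
- **Overview** makes CSF collection optional. It does not say how many participants are expected to accept.

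**The concern.** Change from baseline suits mHTT, NfL and GFAP, which are present before treatment. It does not suit the study drug. If the pre-dose sample contains none, the change is simply the week-57 concentration, and the null hypothesis is that people taking felodipine have none of it in their CSF.

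The Introduction sets verapamil aside because it does not cross the blood–brain barrier, and supports felodipine's brain penetrance with mouse data. CSF felodipine is the only listed outcome that bears on drug exposure of the central nervous system in these patients. The useful result is how much drug is there, relative to blood and to dose. A small p-value could be read as evidence of good penetration when it shows only that the level is not zero. With few donors, a p-value above 0.05 could be read as failure to penetrate even though drug was found in every sample.

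**Working it through.** The article gives no power, significance level or expected number of CSF donors for this outcome, so there is no stated figure to reproduce. Two-sided 0.05 is assumed below.

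**Inputs from the article.** 18 participants, six in each of three cohorts with maximum doses of 5, 10 and 20 mg (Treatment allocation and dosing); CSF optional (Overview); terminal half-life 25 hours (Introduction); dosing ends at week 58 (Overview and Table 1).

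**Step 1. The paired test reduces to a one-sample test.** With baseline 0, the change for participant i is the week-57 level Yi, so t = mean(Y) / (SD(Y)/√n) = √n / CV, where CV is the coefficient of variation of the week-57 levels.

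**Step 2. The p-value does not depend on the amount of drug.** Multiplying every Yi by a constant leaves the CV and the signed ranks unchanged. Six simulated levels, multiplied by 1, 0.1 and 0.001, gave t = 5.44, p = 0.0028 and Wilcoxon p = 0.03125 each time. The amount matters only if some samples fall below the assay limit.

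**Step 3. What the p-value does depend on.** If all n week-57 samples are quantifiable, all differences are positive and the exact two-sided Wilcoxon p-value is 2/2^n. Power of the t-test comes from the noncentral t distribution with noncentrality √n/CV. The documents give no CV, so a range is assumed, and the normal approximation is rough at the larger CVs.

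| CSF donors | Wilcoxon p, all quantifiable | t-test power, CV 0.4 | CV 0.6 | CV 1.0 | CV 1.2 |
|---|---|---|---|---|---|
| 4 | 0.125 | 0.90 | 0.61 | 0.29 | 0.22 |
| 6 | 0.031 | 0.997 | 0.90 | 0.51 | 0.38 |
| 9 | 0.0039 | 1.00 | 0.99 | 0.75 | 0.59 |
| 12 | 0.0005 | 1.00 | 1.00 | 0.88 | 0.75 |
| 18 | 0.000008 | 1.00 | 1.00 | 0.98 | 0.92 |

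With 5 donors the Wilcoxon p-value is 2/32 = 0.0625. The Wilcoxon test therefore cannot reach 0.05 with 4 or 5 donors. If testing is done within a cohort, it can do so only if all six members give both samples and all six week-57 samples are quantifiable (2/64 = 0.031).

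**Step 4. Dose adds to the spread if cohorts are pooled.** The article does not say whether the test is pooled. If levels were proportional to dose (an assumption), six each at 5, 10 and 20 mg have mean 11.67 and SD √(700/17) = 6.42. Dose alone then contributes a CV of 6.42/11.67 = 0.55.

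**Step 5. The stated blood outcome cannot be matched to the CSF outcome.** Week 58 to week 62 is 28 × 24 = 672 hours. 672/25 = 26.9 half-lives, and 0.5^26.88 ≈ 8 × 10⁻⁹ of the drug remains. A CSF:plasma ratio needs the week-57 blood, which is already scheduled.

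**The case against.** The strongest reply is that the outcome still yields what is wanted. All exploratory outcomes are to be summarised as well as tested, and data are summarised by cohort. With a zero baseline, the summary of change is the summary of week-57 concentration. Whether felodipine is detectable in human CSF is also a real question, since the Introduction relies on mice, and the 2/2^n figures assume that every sample is quantifiable. They describe only the sensitivity analysis; the primary t-test does respond to between-patient spread. All of this stands. It confines the point to the significance test and makes it minor.

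Four stronger readings are tempting, but the documents do not support them:

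- *The baseline is zero by design in everyone.* The eligibility criteria are in a figure that is not shown. The visible text on other medicines says only "Participants on any medications that contraindicate the use of felodipine will be excluded from participating in the trial" and does not mention prior felodipine use. Zero is a strong inference, not a documented rule.
- *The outcome is uninformative.* The level is informative; the p-value is not.
- *The plan wrongly omits a CSF:plasma ratio.* The article is a condensed account, the analysis plan is not shown, and FELL-HD-s has its own ethics approval and full documentation. A ratio may be defined there, so its absence here is no defect.
- *The rule "In all analyses, no imputation will be performed" leaves the paired change undefined.* That follows only if below-limit results are recorded as missing. They are censored values, and nothing says they will be dropped.

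**Conclusion.** The point holds for the significance test only. As stated, the article tests an on-treatment drug level against a pre-dose value expected to be zero. The resulting p-value is unaffected by the amount of drug in CSF as long as the samples are quantifiable. It is governed by uptake of the optional lumbar puncture and by between-patient spread: the Wilcoxon p-value runs from 0.125 with 4 donors to 0.000008 with all 18, and at 6 donors the power of the t-test runs from 0.997 to 0.38 across the assumed CVs.

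This rests on participants not already taking felodipine at baseline. The Wilcoxon figures further assume that all week-57 samples are quantifiable, and the power figures rest on the assumed CVs. Severity is minor: this is one exploratory outcome from an optional procedure in an associated sample study, its level will be summarised in any case, and the primary safety outcome is unaffected. It is worth correcting because a better analysis is available from samples already planned.

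**What to change.** In the analysis plan and the FELL-HD-s documents:

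- Omit the significance test for felodipine level. The paired tests for mHTT, NfL and GFAP are outside this point.
- Report the week-57 CSF concentration, the proportion of samples quantifiable, and the CSF:plasma ratio using week-57 blood. The week-62 blood outcome cannot serve for the ratio.
- Summarise by the dose actually being taken at sampling. Treatment allocation and dosing allows participants to be moved back to a lower dose, so allocated cohort may not describe exposure.
- Use the baseline CSF sample as an assay blank and report below-limit values as such.

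**Cost.** No additional samples or visits. Time since last dose has to be recorded for both week-57 samples, and the wording of the outcome and its analysis changes. This can be done when the analysis plan is finalised.

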### Sample size calculation

As this is the first trial to investigate felodipine in patients with HD, there are insufficient data to conduct a formal assessment of the anticipated effect size. The preliminary data from this trial will provide the necessary information to design a further phase 3 trial that is sufficiently powered to show this.

### Trial procedures

#### Clinical

All clinical visits will take place at the John Van Geest Centre for Brain Repair in Cambridge, UK. Clinical measures assessing motor and non-motor features of HD will be performed at screening, baseline and every 8 weeks thereafter up to week 40. After this time point, these clinical assessments will then be repeated at week 57 and at the end of the trial at week 62. The schedule of assessments is summarised in online supplemental table 2.

The Unified Huntington’s Disease Rating Scale (UHDRS) is a clinical rating scale used to assess four domains of clinical performance and capacity in HD; motor and cognitive function, behavioural abnormalities and functional capacity. The assessment has been validated and appears to be appropriate for repeated administration during clinical studies.^11^ Assessments include total functional capacity, diagnostic confidence level, total motor score (TMS), functional assessment and a battery of cognitive tests. Where participants consent, the UHDRS TMS section only may be video recorded at baseline and week 62, enabling validation of the scoring by an independent assessor to check inter-rater reliability.

Cognition will be assessed using the Addenbrookes Cognitive Examination III (ACE-III) which is a neuropsychological test used to identify cognitive impairment. The ACE-III provides a global measure of cognition as well as subscores in five domains: attention and orientation, memory, fluency, language and visuospatial function.^12^ This test will be used throughout the trial but at the screening visit, it will be used to confirm the participant’s capacity to consent.

Other non-motor aspects of HD will be evaluated using the Problem Behaviours Assessment-short), which is a semistructured interview used to rate behavioural symptoms of HD. The assessment looks at depression, anxiety, irritability, aggression, apathy, perseverative thinking, obsessive–compulsive behaviours, delusions, hallucinations, disorientation and will be administered by a trained member of the trial team.^13^ We will also use the Columbia Suicide Severity Rating Scale to rate if there is any suicidal ideation and behaviour on a scale ranging from ‘wish to be dead’ to ‘active suicidal ideation with a specific plan and intent’, participants will answer yes or no to the questions and any that have an answer of yes, more details will be captured. This assessment will be administered by a trained member of the trial team.^14^ Finally, the Hospital Anxiety and Depression Scale will be used which is a self-rating scale to measure anxiety and depression.^15^

Vital signs will be assessed closely, in particular, measurement of blood pressure due to felodipine being an antihypertensive drug. Vital signs (blood pressure, pulse, respiratory rate and body temperature) will be measured at all clinic visits. Participants will also be asked to take weekly blood pressure readings at home and complete a diary that will be reviewed at all clinic visits by the trial team. Participants will be required to inform the trial team if blood pressure readings drop below 90/60 mm Hg or if they experience symptoms of low blood pressure, where further monitoring may be required as decided by the trial team.

Participants’ concomitant medications will be recorded while they are on the trial (including any dose changes), and participants may continue to take all regular medications as prescribed. Participants on any medications that contraindicate the use of felodipine will be excluded from participating in the trial.

#### MRI

The MRI will be an optional component of the trial and, if participants consent to this, an MRI will be performed at baseline (week 0) and at the end of the trial (week 62). Scanning will be conducted on a 3T MRI scanner at the Wolfson Brain Imaging Centre in Cambridge. Each scan will take approximately 1 hour. The scans will be used to assess whether there are any changes in the volume of the caudate nucleus, putamen and whole brain as well as assessing white matter integrity. Given that some participants may struggle to complete the MRI, if they consent to this procedure but would like some sedation, this will be offered to the participant.

#### Biosample collection and processing

As part of the FELL-HD trial, full blood count, liver function tests and urea and electrolytes samples will be taken at every clinic visit and analysed at the Laboratory Research Services in Addenbrooke’s Hospital.

If participants also consent to the FELL-HD-s substudy, 7.5 mL of blood will be collected and tested for HIV, HBV and HCV status to confirm eligibility. Starting at the baseline (week 0) visit and every 8 weeks up to week 40 and then at week 57 and week 62, up to 75 mL of blood will be collected for analysis of markers of disease, as well as levels of felodipine in the blood.

Samples will be taken in two different types of blood collection tubes depending on which laboratories the specimens will be sent to. Two samples will be taken in 8 mL sodium heparin cell preparation tubes and centrifuged at centrifugal force (RCF) 1500×g for 30 min at room temperature for extraction of plasma. Three samples will be taken in 6 mL K2E blood collection tubes and centrifuged at RCF 1300×g for 10 min at 4°C for extraction of plasma.

If consented, CSF will be collected via lumbar puncture at baseline (week 0) before treatment commences and week 57, 1 week prior to the end of treatment. The CSF will be used to assess levels of felodipine, NfL, mHTT and GFAP. CSF will be centrifuged at RCF 400×g for 10 min at 4°C. After spinning, the CSF supernatant will be separated from the CSF cells and stored.

All aliquots for blood and CSF will be stored at −80°C until the end of the trial where they will then be sent to the analysing laboratory which will look at the above protein levels.

### Treatment allocation and dosing

Participants will be assigned to one of three dosing cohorts. Cohort 1 will receive a total of 5 mg daily, cohort 2 will receive a total of 10 mg daily and cohort 3 will receive a total of 20 mg daily. There will be six participants assigned to each cohort in an alternating fashion, that is, participant 1 will be allocated to cohort 1, participant 2 will be allocated to cohort 2, participant 3 will be allocated to cohort 3, participant 4 will be allocated to cohort 1 and so on. This will be performed by the trial coordinator.

All participants will start on 2.5 mg from baseline (week 0), if tolerated, all participants will have their dose increased to 5 mg at week 2 and cohort 1 will then remain on 5 mg until week 58. Those assigned to cohort 2 will have their dose, if tolerated, increased again to 10 mg at week 4 and will remain on 10 mg until week 58. Those assigned to cohort 3 will also have their dose increased to 10 mg at week 4 and then have their dose, if tolerated, increased for a third time to 20 mg at week 6 and will remain on 20 mg until week 58. Please refer to the dosing schedule in table 1.

The dose will only be increased where the previous dose has been tolerated, all judgements of intolerance will be at the PI discretion. Intolerance may be defined by an occurrence of an AE of moderate severity, which is either definitely or probably related to the felodipine. If a participant is unable to tolerate a dose, they will be moved back to the last dose they were able to tolerate within their cohort dosing. If the participant is already at the lowest dose then felodipine will be withdrawn. No dose rechallenge will be undertaken if a dose is reduced during the course of the trial.

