**Methods and analysis:**

FELL-HD is a phase II, single-centre, open-label, dose-finding trial in people with early HD. 18 participants with early clinical features of the disease will be treated with felodipine for 58 weeks, with a further 4-week follow-up. The primary outcome measure is the number of adverse events attributable to felodipine. Exploratory outcomes include additional measures of motor and cognitive function, non-motor symptoms and quality of life scales, as well as peripheral and central disease biomarkers assessed through brain MRI. Analysis of blood and cerebrospinal fluid will also be performed through an associated sample study, FELL HD-s.

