## Methods and analysis

### Overview

FELL-HD is a phase II, open-label trial in people with early HD that aims to test the safety and tolerability of different doses of felodipine. The trial will investigate whether three different doses of felodipine are tolerated over a 58-week treatment period, followed by a 4-week washout follow-up period.

18 participants will be recruited and allocated to one of three cohorts in alternating fashion that will all receive felodipine. All participants will begin on 2.5 mg of felodipine with the dose being increased every 2 weeks from baseline to the cohort maximum dose, only if the previous dose has been tolerated. Cohort 1 will receive a maximum of 5 mg, cohort 2 will receive a maximum of 10 mg and cohort 3 will receive a maximum of 20 mg. The dosing schedule is summarised in table 1. Safety assessments will be performed every 2 weeks up to week 8 while participants reach their maximum allocated dose. Following this, clinical and safety assessments will be performed every 8 weeks until week 40. At week 48, a telephone visit will be performed and participants will then be seen at week 57 for safety and clinical assessments. A repeat telephone visit will be performed at week 58 which is when participants will end their treatment phase with felodipine. Clinical and safety assessments will then be performed at week 62 for the final trial visit. For the schedule of visits, refer to figure 1.

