### Participant identification

Participants will be recruited from a single site in Cambridge, UK. Potential participants will be identified via the NHS HD clinic and from the database of people who have previously attended the NHS HD clinic. These will only be people who have indicated they are interested in being contacted about involvement in future research. The database holds detailed information about demographics, HD status and clinical assessments, comorbidities and medication that will assist in identifying potential participants that fit the inclusion/exclusion criteria as outlined in figure 2.

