**Figure 2 F2:**
[figure not shown]
Inclusion/exclusion criteria. ACE-III, Addenbrookes Cognitive Examination III; HD, Huntington’s disease; MMSE, Mini Mental State Examination.

Alternatively, participants may be asked if they would be interested in the trial at their routine NHS HD clinic appointment.

All interested participants will be provided with a participant information sheet and after approximately 2 weeks (to give them sufficient time to consider the invitation), the trial team will contact them by telephone to see if they would like to participate. If the potential participant is interested, they will be invited to a screening visit where the participant’s understanding of the trial is confirmed and written informed consent is obtained before confirming eligibility through screening assessments. Informed consent will be taken by the principal investigator (PI) or subinvestigator (SI). However, if a potential participant is not interested, they will continue with their standard clinical care.

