### Trial monitoring and oversight

FELL-HD is jointly sponsored by Cambridge University Hospitals NHS Foundation Trust and University of Cambridge. The Sponsor will assign a Clinical Trials Monitor who will monitor the trial team to ensure they are adhering to the protocol and regulatory requirements. The first monitoring visit will take place within 10 working days of the first participant commencing treatment. Monitoring will then take place regularly until the trial ends. Any changes to the monitoring plan will be updated in the monitoring plan agreement and risk assessment form associated with the FELL-HD trial.

There will be a Trial Management Group (TMG) consisting of the chief investigator, SI, trial coordinators, trial pharmacist, trial statistician and clinical trial monitor who will meet once a month to discuss the running of the trial.

There will also be a Trial Steering Committee (TSC), which is a multidisciplinary group comprising members who are jointly responsible for the overall supervision of the FELL-HD trial. This committee will include but is not limited to the members of the TMG, an independent chair, independent clinical or scientific experts, independent statisticians with relevant experience and representatives of people with lived experience of HD. The TSC will meet at least every 12 months while participants are receiving felodipine and at least once thereafter.

All trial documentation and any amendments will be reviewed by the sponsor and approved for submission to the relevant regulatory bodies. Once full approval has been received, the information will be communicated as appropriate with the trial team, TMG and TSC.

All personal data are stored on the University of Cambridge Secure Data Hosting Service, this is password protected and can only be accessed by the immediate trial team. All data entered into the electronic database are anonymised and entered under a specific participant trial ID for the wider trial team to access.

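### Cohorts are filled by open, fixed alternation, so recruiting staff can predict the next dose cohort; this can bias the descriptive comparison of felodipine-related AEs between doses.

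*Protocol article*

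**What the plan says.** The Overview states that "18 participants will be recruited and allocated to one of three cohorts in alternating fashion that will all receive felodipine". Treatment allocation and dosing repeats this ("There will be six participants assigned to each cohort in an alternating fashion") and spells out the sequence: "participant 1 will be allocated to cohort 1, participant 2 will be allocated to cohort 2, participant 3 will be allocated to cohort 3", with participant 4 returning to cohort 1. On who carries it out, it says: "This will be performed by the trial coordinator". No random element and no concealment step is described.

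The setting is given in the abstract: "FELL-HD is a phase II, single-centre, open-label, dose-finding trial in people with early HD". Under Participant identification, candidates are found through the clinic and its database: "The database holds detailed information about demographics, HD status and clinical assessments, comorbidities and medication". The PI or an SI takes consent at the screening visit, and eligibility is confirmed after that. Eligibility criteria adds that screening reviews medical history and vital signs. The coordinators belong to the Trial Management Group, "consisting of the chief investigator, SI, trial coordinators, trial pharmacist, trial statistician and clinical trial monitor who will meet once a month".

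Under Statistical methods, the primary outcome (the number of AEs attributable to felodipine) is summarised descriptively by dosage for each cohort, participants are analysed in their allocated cohort, and the primary endpoint has no hypothesis test. The exploratory endpoints are tested within participants, baseline against week 57/62.

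**The concern.** With a fixed sequence, the next cohort can be read from the number of people already entered. The staff who can read it also know, or soon learn, each candidate's comorbidities, medication and vital signs. The Clinical procedures section singles out blood pressure for close monitoring because felodipine is an antihypertensive, so a visible baseline feature could plausibly relate to the primary outcome. A cautious clinician who delays or brings forward an invitation according to the next slot would make the cohorts differ in more than dose. This needs no misconduct.

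At stake is how AEs at 5, 10 and 20 mg are read against each other. The trial calls itself dose-finding, and the Sample size calculation section says its data will inform a phase 3 design. The absence of a hypothesis test does not protect a descriptive contrast from confounding. The limitations listed after the abstract name the open label and the small numbers, but not predictable allocation.

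**Working it through.** **1. The plan's own figure.** Three cohorts of six: 3 × 6 = 18. The rule cohort = ((i − 1) mod 3) + 1 for i = 1 to 18 gives 6/6/6, as stated. Cohort 3 takes entries 3, 6, 9, 12, 15 and 18. There is no alpha, power or effect size to reproduce.

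**2. Predictability of the next cohort.** Under alternation there is one possible sequence, so 18 of 18 are predictable. The number of possible random 6/6/6 sequences is 18!/(6!)³ = 17,153,136.

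Past allocations are visible in an open-label trial, so suppose staff know all of them, and any block size, and always guess the cohort with most places left. With a, b, c places left, the expected number of correct guesses is

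E(a,b,c) = max(a,b,c)/(a+b+c) + Σ [places left in a cohort/(a+b+c)] × E(after one place in that cohort is used).

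- Blocks of 3: 1/3 + 1/2 + 1 = 1.833 per block; × 6 blocks = 11.0 of 18 (61%).
- Blocks of 6: 3.367 per block; × 3 blocks = 10.1 of 18 (56%).
- One permutation of 18: 8.7 of 18 (49%).
- Simple randomisation: 18/3 = 6 of 18 (33%), but group sizes of 6/6/6 are then not guaranteed.

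**3. What steering could do (assumption, not in the documents).** Let there be no true dose effect. When staff foresee a cohort 3 slot, they enter someone whose expected number of felodipine-related AEs is lower by s; when they foresee a cohort 1 slot, higher by s. Under alternation the spurious difference, cohort 3 minus cohort 1, is −s − s = −2s per participant, or 6 × (−2s) = −12s in the cohort totals.

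For the random lists, staff are assumed to act only when a single cohort has most places left (simulation, 20,000 runs).

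| Allocation | s = 0.10, per participant | s = 0.20, per participant | Cohort totals (× 6) |
|---|---|---|---|
| Alternation | −0.20 | −0.40 | −1.2; −2.4 |
| Blocks of 3 | −0.067 | −0.133 | −0.4; −0.8 |
| Blocks of 6 | −0.057 | −0.114 | −0.3; −0.7 |
| One permutation of 18 | −0.040 | −0.080 | −0.2; −0.5 |
| Simple randomisation | 0 | 0 | 0 |

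If staff steer the other way, every sign reverses.

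**4. Is alternation needed?** According to Table 1 and Treatment allocation and dosing, every participant starts at 2.5 mg and is titrated individually. The cohorts recruit in parallel and none waits for another to be cleared. No stated step depends on the order in which cohorts are filled.

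**The case against.** Several stronger readings are tempting, and the document does not support them.

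- *A reader might infer that the trial's only comparison is compromised.* It is the only between-group one. The planned paired tests are the only formal tests, and a within-participant change does not rest on the cohorts being comparable. Dose information also arises within people: everyone passes through 2.5 and 5 mg, and cohorts 2 and 3 both reach 10 mg. That information is short-term, so the long-term contrast still rests on the cohorts.
- *A reader might infer that each person's dose is known before consent.* The article does not say when a participant number is given. If numbers follow confirmed eligibility, screen failures and overlapping screening could change who takes which slot. The next open slot is predictable; a named candidate's slot at consent may not be.
- *A reader might infer that AEs at 20 mg will be understated.* Nothing gives the direction or size of any steering, or shows that it happens.
- *A reader might size the problem as one person in six, about 17 percentage points.* That describes the proportion of participants with an AE, whereas the primary outcome is a number of AEs.

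It is also fair to say that the trial does not claim to be randomised or confirmatory, that chance imbalance at six per cohort would persist under any scheme, and that concealment does not cure open-label attribution of AEs. Alternation also has a merit: it spaces cohort 3 entries evenly. Under one random permutation, the first entrant falls in cohort 3 with probability 1/3, and the first three all do with probability (6 × 5 × 4)/(18 × 17 × 16) = 120/4,896 = 2.5%. The document does not give spacing as a reason for alternating.

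These points limit the concern. They do not remove it: predictable allocation is a stated method here, not a detail left to another document, and it can be avoided.

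**Conclusion.** The concern holds in a limited form. Fixed alternation makes the next cohort predictable 18 times out of 18 to the staff who select, consent and confirm eligibility, and this can bias the descriptive comparison of felodipine-related AEs between dose cohorts. With past allocations and any block size known, a random 6/6/6 list would bring that down to 49–61%, depending on the type of list. This rests on staff knowing how many participants have entered, which a single-centre team meeting monthly with the coordinators can be expected to know. The size and direction of any bias cannot be derived from the document; the −2s illustration depends wholly on an assumed s.

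**What to change.** Replace alternation with a concealed random 6/6/6 list, prepared by a statistician and held by someone with no part in recruitment. Release one assignment at a time to the coordinator, only after consent and confirmed eligibility. One permutation of 18 is the least predictable (49%). Blocks keep entries more evenly spaced but are easier to guess (56% for blocks of 6, 61% for blocks of 3, if the block size is known), so any block size should be withheld from recruiting staff. Because the analysis population refers to replaced participants, the list should also state which cohort a replacement joins, unless the full protocol already does.

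If recruitment has begun, apply the list to the remaining slots. If it is complete, report predictable allocation as a limitation of the between-dose comparison and show baseline characteristics by cohort; the planned summaries by cohort can carry these.

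The cost is one list and a short amendment, with less even calendar-time balance and less even spacing of entries to the highest-dose cohort, both milder with blocks. The sample size of 18 and the dosing schedule do not change.
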